**Chaplains**

- 1. **Demographic and attitudes toward CBCT**
- (3 min) **Interest in CBCT Survey**: will assess interest with and experience in meditation and yoga and expectancy.
- (4 min) **Demographic scale**: asks age, ethnicity, marriage status, number and ages of children, and housing status
- **Adoption:** We adapted a scale previously used[^12^](#_ENREF_12) to measure practitioner attitudes and intent to deliver an intervention. The scale includes 6 attitude items (i.e., 3 Positive Outcome and 3 Negative Process) as well as 6 items on organizational barriers to adoption of evidence-based practices. These 12 items are rated on a 5-point Likert scale from 1 (strongly disagree) to 5 (strongly agree).
- (2 min) **Attitudes about empathy scale**[**^13^**](#_ENREF_13): a 6-item likert scale questionnaire that asks people to rate their agreement with statements about the nature of empathy.
  1. **Resilience**
- (4 min) **The Depression Anxiety and Stress Scale (DASS**)[**^14^**](#_ENREF_14): is a 42-item likert-scale measure that assesses the frequency of symptoms of depression, anxiety and stress during the past week.
- (2 min) **Mental Health Continuum Short Form (MHC-SF**)[^15^](#_ENREF_15): a 14-item inventory assessing emotional well-being (<http://calmhsa.org/wp-content/uploads/2013/06/MHC-SFEnglish.pdf>)
- (4 min) **Professional Quality of Life Scale (ProQOL)**[^16^](#_ENREF_16): a 30-item inventory, the ProQOL is the most commonly used measure of the negative and positive effects of helping others who experience suffering. It has sub-scales for compassion satisfaction, burnout, and compassion fatigue.
- (2 min) **School-Burnout Inventory (SBI)**[**^17^**](#_ENREF_17)**:** a 9-item inventory that measures burnout in the context of an academic environment.
- **(6 min) Tellegen Absorption Scale (TAS)**[**^18^**](#_ENREF_18)**:** a 34-item inventory measuring openness to absorbing and self-altering experiences.
- **(3 min) Sensed Presence Questionnaire (SenPQ)**[**^19^**](#_ENREF_19)**:** a 16-item likert-scale measure assessing recent experiences of subjective feelings that an entity, individual, or being is present in the absence of clear sensory evidence. Responses to this scale has been shown to vary with meditation practice.
  1. **Compassion and Empathy**
- (15 min) **Empathic Accuracy (EA) Task**[**^8^**](#_ENREF_8)**:** a dynamic video assessment that asks subjects to continuously rate the emotions of others as they tell emotional autobiographical stories.
- (2 min) **Spiritual Meaning Scale (SMS)**[^20^](#_ENREF_20): a 15-item, likert-scale inventory that assesses the extent to which someone endorses a belief in something larger than themselves.
- (4 min) **Jefferson Scale of Empathy**[^21^](#_ENREF_21)^,^[^22^](#_ENREF_22): a 20-item scale designed to measure empathy in practicing health care professionals and health care professional students. It has been translated into 53 languages and has been used in more than 80 countries.

Total time required for completion of measures is approximately 45 minutes. All measures will be delivered digitally.

- 1. **Post Patient Consult Checklists**
- (2-4 min) **Post-Visit Checklist for CBCT:** a 41-item checklist that assesses the encounter the CBCT-trained Chaplain Resident had with the patient; including how/if the Resident prepared for the consult, assessed the patient’s state of mind, used specific tools and skills during the consult, and how well the Resident thought the encounter went.
- (2 min) **Post-Visit Checklist for non-CBCT:** a 17-item checklist that assesses the encounter the non-CBCT-trained Chaplain Resident had with the patient; including how/if the Resident prepared for the consult, assessed the patient’s state of mind, used specific tools and skills during the consult, and how well the Resident thought the encounter went.

**Patients**

- (<1 min) **NCNN Distress Thermometer**[**^23^**](#_ENREF_23)**:** a single-item distress thermometer that compares favorably with longer measures used to screen for distress.
- (1 min) **PROMIS Self-Efficacy for Managing Emotions**[**^24^**](#_ENREF_24)**:** a likert-27-item scale that measures a subject’s level of confidence to manage and control symptoms of anxiety, depression, helplessness, discouragement, frustration, disappointment, and anger.
- (2 min) **PROMIS Positive Affect**[**^25^**](#_ENREF_25)**:** a 15-item likert-scale that asseses momentary positive or rewarding affective experiences such as feelings and mood associated with pleasure, joy, elation, contentment, pride, affection, happiness, engagement and excitement.
- (4 min) **Hospital Anxiety and Depression Scale (HADS)**[**^26^**](#_ENREF_26)**:** a 14-item questionnaire that is widely used for detecting anxiety and depressive disorders.
- (2 min) **PROMIS Emotional Support**[**^27^**](#_ENREF_27)**:** a 4-item likert-scale that assessed perceived feelings of being cared for and valued as a person.
- (2 min) **PROMIS Informational Support**[**^28^**](#_ENREF_28)**:** a 4-item likert-scale that assesses perceived availability of helpful information or advice.
- (2 min) **PROMIS Social Isolation**[**^29^**](#_ENREF_29)**:** a 4-item likert-scale that assesses perceptions of being avoided, excluded, detached, disconnected from, or unknown by, others.
- (4 min) **Scottish Patient Reported Outcome Measure (PROM)**[**^30^**](#_ENREF_30)**:** an 18-item likert-scale that assesses how a hospitalized patient felt about the Pastoral Care visit both during the consult and after it. It also assesses the patients present state regarding their situation and whether they see themselves as a spiritual or religious person.

For the post-CBCT assessments (T1 for the early-start group, and T3 for the delayed-start group), in addition to the questionnaires listed above we will also ask participants to complete a questionnaire regarding their experiences with CBCT. This questionnaire will take approximately 2-4 minutes to complete. A subset of the chaplain residents will be interviewed at three time points relative to their training in CBCT. The interviews consist of open-ended questions to further query their learning experiences with CBCT. We will also collect anonymized curriculum materials completed by chaplain residents enrolled in the study. Curriculum material will be coded with a subject ID and will not be linked to personal identifiers when researchers are analyzing the data.

**Audio Recordings:**

Chaplain residents will wear a recording device that will record chaplain-patient interactions. Patients will be informed that they can stop the recording at any time and that they can ask for their recording to be deleted at any time if they no longer wish for it to be a part of the study. Audio recordings will be de-identified, such that patient and chaplain are only linked with participant IDs and identity will not be available to anyone coding the recordings. Patients and chaplain participants will complete an assent form to indicate how their recordings can be used, including whether recordings can be used for other research projects by our team, by other researchers, and for scientific presentation of these data.

1. **Data analysis**

We will analyze the data to test the hypothesis that CBCT improves chaplain residents’ empathic accuracy and resilience in a hospital setting. SAS 9.4 and SPSS 23 will be used to conduct statistical analysis of the collected data. Descriptive statistics will be used to describe selected characteristics of participants by group, expressed as frequencies and percentages. The primary outcomes of empathic accuracy, compassion fatigue, compassion satisfaction, empathy, anxiety, and depressive mood will be measured as pre-to-post differences in the measurement scores, i.e., T1 – T0. For the early-start group and T3 – T2 for the delayed-start group. We will examine the effect of CBCT by analyzing the correlated, repeated-measure data (T1 – T0) – (T3 – T2) using mixed linear models, implemented in SAS Proc Mixed. Mean pre-to-post differences will be compared across groups.

To evaluate whether the effects of CBCT persist over time, differences between mean scores on measures of empathic accuracy and resilience for the early-care group will be compared across four time points: from baseline measurement to early-group post-CBCT measurement (T1 – T0), from early-group post-CBCT measurement to delayed-group pre-CBCT measurement (T2 – T1)_,_ and from delayed-group pre-CBCT measurement to delayed-group post-CBCT measurement (T3 - T2). To evaluate whether the effects of CBCT depend on the timing of program delivery, the differences between mean scores on empathic accuracy and resilience will be compared for each group during the period following receipt of the CBCT program; that is, (T1 – T0) – (T3 – T2).

To evaluate whether CBCT-informed interventions improve patient outcomes, descriptive statistics (means, standard deviation, standard error) will be used to characterize baseline demographics and responses to self-report assessments. All data will be evaluated for normality, and appropriate procedures will be performed in cases where normality is violated. To evaluate whether CBCT-informed spiritual consults impact patients’ negative symptoms, well-being, and patient health outcomes (duration of stay and patients’ Press Ganey satisfaction scores) we will conduct independent samples t-tests. Dichotomous variables (denial of treatment, opioid use) will be evaluated using chi square tests.

To explore chaplain and patient mediators of the impact of spiritual care consults on patient outcomes, chaplain resident, patient, and chaplain-patient interactions will be tested in mediation analyses using linear regression analysis in order to examine which factors account for improvement in patient outcomes (opioid use, duration of stay, denial of care, patient satisfaction). Any chaplain variables (empathic accuracy or self-reported compassion) that are impacted by CBCT, or patient variables (negative symptoms, well-being) that are impacted by CBCT-informed modules will be entered as independent variables into linear regression analysis with group assignment, and with patient health outcomes as the dependent variable in order to examine whether chaplain, patient, or chaplain-patient interaction variables render group assignment insignificant in accounting for variance in patient health outcomes[^31^](#_ENREF_31).

1. **Compensation:**

No compensation will be provided to participants.

1. **Risks to participation:**

Chaplain residents and Emory Healthcare patients may experience some emotional discomfort while completing the questionnaires. To minimize this risk, all participants will be informed that they are free to skip any questions that are upsetting and that they can stop the questions at any time. In addition, they will be provided help in contacting the Emory Faculty and Staff Assistance Program (FSAP).

In addition, the questionnaires that subjects will fill out as part of this study will contain personal information, and participants may have private pieces of audio recorded.

We acknowledge that it could be embarrassing if this information were to become public or fall into the hands of someone not associated with the study. We will take steps to prevent this from happening. All self-report data will be de-identified and stored by a study number, such that these data will be anonymous at all times during data entry and analysis. In addition, all data, including personal identifiers (i.e. name, address, email contact details), will be maintained in secure password-protected electronic files stored on a secure computer system that can only be accessed by study researchers.

1. **Procedures for minimizing risks:**

To minimize the risk that participants become upset while completing questionnaires, the residents will be informed that they are free to skip any questions that are upsetting and that they can stop the questions at any time. In addition, they will be provided help in contacting the Emory Faculty and Staff Assistance Program (FSAP).

Personal identifiers (i.e. name, address, email contact details) will be maintained in secure password-protected electronic files. All of the data collected for these studies will be kept strictly confidential. Under no circumstances will individually identifiable data be released to anyone without the written consent of the subject. Emory Healthcare administrators will not have access to questionnaire data. Results will be discussed with the subjects at their request.

1. **Risk-Benefit Ratio:**

Other people may potentially benefit from what this study reveals. It is hoped that such knowledge will ultimately lead to a better understanding of how CBCT affects the spiritual caregiver in a hospital environment and may inform the application of CBCT to improve patient care. These potential benefits outweigh the minimal risk this research poses to subjects.

1. **Data Safety Monitoring Plan:**

Human subjects’ data to be collected includes responses to questionnaires. Subject data will be identified by ID number, with only the PI and IRB-approved personnel working in her lab having access to the list linking subject names and ID #s. This list will be saved as a password-protected computer file. All data will be collected specifically for the purpose of this research project.

All data will be stored on a secure computer system that can only be accessed by study researchers. Questionnaires will be stored by study number and not by subject name. Any paper data will be stored in a locked filing cabinet, to which only investigators in this study will have access. All electronic data will be stored in a password-protected Emory database, which only [name] and the member(s) of the research team assisting with data analysis have access to. The database is monitored by Emory computing services, and any problems or breaches will be directed to [name] attention.

All AEs that occur during the course of the study, either directly related to the CBCT program or unrelated, will be reported to the Emory IRB. Any SAEs will be reported within 24 hours according to standard regulations, and will be reported to funding agencies.

1. **Benefits to subject or future benefits:**

Chaplain residents participating in the study may benefit from the introspection and learning associated with completing the study questionnaires. Chaplain resident participants will also likely benefit from exposure to research methodology as part of their CPE experience.

Other people may potentially benefit from what this study reveals. It is hoped that the knowledge gained will ultimately lead to a better understanding of how CBCT affects the spiritual caregiver in a hospital environment and inform the application of CBCT to improve patient care.

1. **Training:**

All Study personnel are CITI certified and will maintain CITI certification throughout their involvement in the study. Data collection and statistical analyses will be carried out by [name] or her research assistants.

1. **Confidentiality:**

The study will keep any records that are produced private. Study number will be used rather than subject’s name on study records where applicable. Subject’s name and other facts that might point to subject will not appear when this study is presented or results are reported.

1. **Informed consent:**

Written informed consent will be obtained at the Emory Healthcare campuses by [name] or approved study personnel prior to showing the empathic accuracy videos or administering questionnaires.

1. **Plans to inform participants of new findings or research results that might affect health:**

If researchers learn any new information that might affect the risk/benefit ratio for study participation, research subjects will be notified immediately—either in person for subjects still in protocol or by phone and/or email for subjects who have completed or dropped out of the protocol.

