The Emory University Spiritual Health department will incorporate CBCT into their training curriculum using a phased approach beginning in Fall 2017, which provides the opportunity to compare students receiving the CBCT addendum with those receiving traditional chaplaincy training. Here we propose a naturalistic study that examines the impact of incorporating CBCT into Emory’s spiritual caregiver training program. To this end, we will examine the effect of CBCT on empathic accuracy and resilience by comparing the first group of students who receive CBCT-informed training with chaplains who receive standard training in spiritual caregiving and receive CBCT later in the residency year. Data on empathic accuracy will be collected using an existing validated task that measures the degree of correspondence between chaplain-reported emotional states of individuals relaying illness-related experience on video and the emotional states reported by the individuals themselves at the time of video recording[^8^](#_ENREF_8). Data on chaplain resilience will be collected using self-report questionnaires measuring compassion fatigue, compassion satisfaction, empathy, anxiety, and depression.

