**a. Specific Aims**

**Specific Aim 1: To estimate the effect of receiving CBCT on empathic accuracy and resilience among chaplain residents providing spiritual care to hospitalized patients.**

We will conduct a naturalistic study of up to 30 chaplain residents serving the Spiritual Health department of Emory Healthcare, and who will receive CBCT during the first unit of their year-long residency (the early-start group) or approximately midway through the residency year (the delayed-start group). Empathic accuracy and resilience will be measured for all participants before the early-start group receives CBCT (baseline, or T0); after the early-start group completes CBCT (T1); before the delayed-start group receives CBCT (T2), and after the delayed-start group completes CBCT (T3). See **Figure 3** for study schematic. The change in mean score of empathic accuracy and resilience measures from T0 to T1 among participants in the early-start group will be compared to the change in mean score among participants in the delayed-start group over the same time period.

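### For Aim 1 the protocol fixes only a raw change-score comparison; a T0-adjusted estimate and the baseline difference should be reported beside it, because neither estimator is safe alone in groups not stated to be randomised

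*Protocol*

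**What the plan says.** Specific Aim 1 sets the contrast: "The change in mean score of empathic accuracy and resilience measures from T0 to T1 among participants in the early-start group will be compared" with the change in the delayed-start group over the same period. T0 is measured in every participant before the early-start group is trained, so in this contrast T0 is the pre-score of both groups.

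The Data analysis section fixes the outcome scale for the primary chaplain outcomes, which "will be measured as pre-to-post differences in the measurement scores", and the comparison: "Mean pre-to-post differences will be compared across groups". It plans mixed linear models in SAS Proc Mixed, names no covariates, and mentions neither a baseline term nor a common baseline mean.

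On size and assignment, Aim 1 states "We will conduct a naturalistic study of up to 30 chaplain residents". The Background describes a roll-out "using a phased approach beginning in Fall 2017, which provides the opportunity to compare students receiving the CBCT addendum" with those in traditional training. No randomisation to early or delayed start is stated. The Synopsis says that the pilot data will be used to estimate efficacy and inform a randomised trial.

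**The concern.** A change score subtracts the whole of the baseline, as if the slope of T1 on T0 were 1. When the correlation is below 1 and the variances are equal, the slope is smaller and the subtraction adds noise that a covariate would remove. In a study of at most 30 residents that loss can matter.

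The change score also carries any regression to the mean: a group that happens to start worse will appear to improve more. The Aim 1 estimate is meant to feed the planning of a later trial. With a single estimator and no reported baseline difference, a reader could not see how far the estimate depends on where the groups started.

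**Working it through.** **Inputs.** From the protocol: at most 30 residents, T0 and T1 in both groups, change-score comparison. The protocol gives no SD, T0-T1 correlation or group split for this comparison, so there is no planning figure to reproduce. Assumed: n = 15 per group, equal SD at T0 and T1 (SD = 1), correlation r from 0.3 to 0.9.

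**Does the mixed model already adjust?** With T0 and T1 both as responses, complete data and no baseline term or constrained baseline mean, the group-by-time estimate equals the difference in mean change. Naming Proc Mixed does not by itself bring in an adjustment.

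**Precision.** The variance of either estimate is (2/15) times a factor:

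- change score: 2(1 − r)
- T0-adjusted: (1 − r²)(1 + 1/26), where 26 = 30 − 4 and the last term pays for estimating the slope

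| r | Change factor | Adjusted factor | Ratio | Variance reduction |
|---|---|---|---|---|
| 0.3 | 1.400 | 0.945 | 0.675 | about 32% |
| 0.5 | 1.000 | 0.779 | 0.779 | about 22% |
| 0.7 | 0.600 | 0.530 | 0.883 | about 12% |
| 0.9 | 0.200 | 0.197 | 0.987 | about 1% |

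At r = 0.5 the standard error falls from √(2/15 × 1.000) = 0.365 SD to √(2/15 × 0.779) = 0.322 SD.

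The term 1/26 supposes that both groups come from one population. With a systematic 0.5 SD gap it becomes (2/15 + 0.5²)/(2/15 × 26) = 0.383/3.467 = 0.111. At r = 0.5 the ratio is then 0.75 × 1.111/1.000 = 0.833, a reduction of about 17%. At r = 0.9 it is 0.19 × 1.111/0.200 = 1.055, so the gain is gone.

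**Size of a chance gap.** The baseline difference between two groups of 15 from one population has standard error √(2/15) = 0.365 SD. The chance that it exceeds 0.3 SD in either direction is 41%, and that it exceeds 0.5 SD is 17%.

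**Effect of a gap g on each estimate, with no true effect.**

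- *Gap regresses to a common mean.* The expected T1 difference is r·g. The change-score estimate is r·g − g = −(1 − r)g; the adjusted estimate is r·g − r·g = 0.
- *Gap is a stable group difference.* The expected T1 difference is g. The change-score estimate is g − g = 0; the adjusted estimate is g − r·g = +(1 − r)g.

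For g = 0.5 SD, with the means from a simulation of 10,000 runs per case in brackets:

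| Case | r | Change score | Adjusted |
|---|---|---|---|
| Regressing | 0.5 | −0.25 (−0.251) | 0 (0.000) |
| Regressing | 0.7 | −0.15 (−0.155) | 0 (−0.006) |
| Stable | 0.5 | 0 (0.001) | +0.25 (0.248) |
| Stable | 0.7 | 0 (0.001) | +0.15 (0.153) |

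The adjusted estimate minus the change-score estimate always equals (1 − fitted slope) × observed baseline difference. The pair therefore shows how much the answer depends on the baseline, but not which estimate is right.

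**The case against.** The strongest reply is that a comparison of changes is a recognised choice for groups that were not randomised. It is unbiased when the groups differ by a stable amount, which is where the adjusted estimate fails. This stands. A reader might infer that the planned analysis is biased and that a T0 covariate would correct it. The protocol does not support that, because nothing in it says whether a baseline gap would regress or persist. It is therefore no ground for demoting the planned comparison to a sensitivity analysis.

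Second, model covariates are often left to a statistical analysis plan, which is not at hand, and the protocol does not rule them out. This stands in part. A later plan may add T0, but the outcome scale and the comparison are stated choices, and as stated they give the unadjusted contrast.

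Third, in the Data analysis section the outcome sentence runs on to T1 − T0 and then "For the early-start group and T3 – T2 for the delayed-start group". There the delayed-start pre-score is T2. This stands: the T0 covariate fits only the Aim 1 contrast.

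Fourth, the precision gain depends on a correlation that the protocol does not give, and it nearly vanishes at 0.9. This also stands, and is why a range is shown.

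**Conclusion.** The point holds for Specific Aim 1. The protocol states one estimator, the raw T0-to-T1 change, although T0 is collected in everyone. With 15 per group, equal variances and groups from one population, adjusting for T0 lowers the variance by about 32% to 12% at correlations of 0.3 to 0.7, and by about 1% at 0.9. The gain is smaller if the groups differ systematically at T0.

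On bias the two estimators are symmetrical: a 0.5 SD gap at r = 0.5 moves one or the other by about 0.25 SD, depending on whether it regresses or persists. The defect is that a single estimate would hide this dependence, not that the change score is the wrong estimator. Nor do the documents show that a large gap is likely: under chance alone, a gap above 0.5 SD in either direction has probability 17%.

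The point does not extend to the contrast "T1 – T0) – (T3 – T2) using mixed linear models, implemented in SAS Proc Mixed". That contrast compares two trained periods and is given both for the effect of CBCT and for timing, whereas Aim 1 uses the untrained delayed-start group. The two definitions must be reconciled separately, and a baseline covariate does not do it.

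**What to change.** For Aim 1, and for each chaplain outcome, report side by side:

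1. the planned comparison of T1 − T0 between groups;
2. a model of the T1 score on group with the resident's own T0 score as covariate;
3. the T0 difference between groups.

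State in advance that, if the two estimates disagree, the report will say that the result depends on baseline imbalance and will not pick the more favourable one.

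The cost is one covariate, one degree of freedom and a second estimate to interpret per outcome. No new data are needed, and SAS Proc Mixed, already planned, can fit the model. The change should be written against the Specific Aim 1 contrast, and the Data analysis contrast reconciled with Aim 1 as a separate step.

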**Specific Aim 4: To evaluate whether CBCT-informed interventions improve patient outcomes.**

Upon completion of their training program, chaplain residents will provide spiritual consults to patients throughout the Emory hospital system. We will conduct comprehensive assessments in order to examine whether patient (n = 300) outcomes are improved for those receiving chaplain spiritual care augmented by CBCT, in comparison to those receiving spiritual care from chaplains who receive CBCT later in their residency. To this end, study personnel will shadow chaplain residents in both groups and will administer self-report assessments of negative symptomology (depression, anxiety, and loneliness) and well-being (quality of life, hope) to consented patients. In addition, study personnel will audio record chaplain-patient interactions. Patient outcomes will be gathered from retrospective chart reviews and will include use of opioid pain medication, duration of stay, patient’s denial of care, and patients’ Press Ganey satisfaction scores.

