During their training program, chaplain residents will provide spiritual consults to patients throughout the Emory hospital system. We will examine whether patient (n = 300) outcomes are improved for those receiving chaplain spiritual care augmented by CBCT, in comparison to those receiving spiritual care from chaplains who receive CBCT at the end of their residency program. To this end, study personnel will shadow chaplain residents in both groups and will administer self-report assessments of negative symptomology (depression, anxiety, and loneliness) and well-being (quality of life, hope) to consented patients. In addition, study personnel will audio record chaplain-patient interactions. Patient outcomes will be gathered from retrospective chart reviews and will include use of opioid pain medication, duration of stay, patient’s denial of care, and patients’ Press Ganey satisfaction scores.

In a final step, using patient chart reviews we will examine chaplain and patient factors that may mediate the link between spiritual consults and improved patient outcomes. Specifically, we will examine whether chaplain empathic accuracy or self-reported compassion mediate the impact of spiritual care consults on patient health outcomes. We will also examine whether patients’ well-being (hope, quality of life), or negative symptoms (depression, anxiety, loneliness) mediate the impact of spiritual care consults on patient health outcomes.

We will also use the ambulatory ambulatory audio recordings of the chaplain-patient interactions to interrogate which aspects of the chaplain-patient interaction mediate improved patient outcomes (see Figure 4). Spiritual consult audio recordings will be coded by 2 trained, independent CBCT instructors for CBCT content. They will also be coded for linguistic and behavioral elements derived from existing models of compassionate interaction in the hospital environment[^9^](#_ENREF_9).

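### Aim 5 admits only chaplain measures that CBCT has changed, but the Data analysis contrast for that effect subtracts one CBCT gain from another

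*Protocol*

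**What the plan says.** Three parts of the protocol bear on this point.

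- **Data analysis, chaplain outcomes.** The primary chaplain outcomes, empathic accuracy among them, are pre-to-post differences: "T1 – T0. For the early-start group and T3 – T2 for the delayed-start group". The effect is then examined as follows: "We will examine the effect of CBCT by analyzing the correlated, repeated-measure data (T1 – T0) – (T3 – T2) using mixed linear models". The same expression returns at the end of that part as the test of whether timing matters.
- **Data analysis, mediation.** The candidates for the regression are "Any chaplain variables (empathic accuracy or self-reported compassion) that are impacted by CBCT". Mediation is judged by whether they "render group assignment insignificant in accounting for variance in patient health outcomes". Procedures describes the aim in similar terms: "we will examine whether chaplain empathic accuracy or self-reported compassion mediate the impact of spiritual care consults on patient health outcomes". Neither place names a visit or a change score for the mediator.
- **Specific Aims.** Aim 1 compares the T0-to-T1 change in the early-start group with the change in the delayed-start group over that same interval. Aim 4 compares patients of CBCT-trained chaplains with patients of chaplains who have yet to be trained: "in comparison to those receiving spiritual care from chaplains who receive CBCT later in their residency".

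**The concern.** A mediation analysis needs a group-to-mediator step: does assignment to early CBCT move the chaplain measure relative to chaplains who have not had CBCT? The Data analysis section makes this step a condition of entry. The only contrast that the section gives for the CBCT effect sets the early group's CBCT gain against the delayed group's CBCT gain. That is the right contrast for Aim 3 and the wrong one for deciding whether CBCT changed the measure.

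The risk is a false negative. Empathic accuracy could carry the whole patient effect and still be kept out of the model because early and late training worked equally well. The Synopsis says the pilot data are to inform a randomized trial, so a wrong finding of no chaplain mediation would carry forward.

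**Working it through.** The protocol states no effect size, SD, significance level or power, so there is no figure of its own to reproduce.

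**1. What each contrast estimates.** Let δE and δL be the early and delayed CBCT gains. Let dA and dB be the drift due to residency itself over T0–T1 and T2–T3, assumed common to both groups.

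- Data analysis: (δE + dA) − (δL + dB) = (δE − δL) + (dA − dB)
- Aim 1: (δE + dA) − dA = δE

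The first is zero when δE = δL and drift is equal. It equals δE only if delayed CBCT does nothing and drift is equal.

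**2. Effect on the screen.** Assumptions: 15 chaplains per group (the protocol gives up to 30 and no split), score variance 1, within-chaplain correlation 0.6, early effect 0.8 SD, no drift, two-sided 5% test.

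- SD of a change = √(2 × (1 − 0.6)) = 0.894
- SE of the group difference = 0.894 × √(2/15) = 0.327
- Aim 1: 0.8/0.327 = 2.45, so power is about Φ(2.45 − 1.96) = 0.69 by normal approximation; the simulated t-test gives 65.5%
- Data analysis contrast with equal effects: 0/0.327 = 0, so only the 5% false-positive rate remains; simulated 4.9%

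Results of 3,000 simulated trials per row:

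| Late ÷ early effect | Expected Data analysis contrast (SD) | Passes, Data analysis contrast | Passes, Aim 1 contrast |
|---|---|---|---|
| 0 | 0.8 | 64.9% | 65.8% |
| 0.5 | 0.4 | 22.0% | 65.8% |
| 1 | 0 | 4.9% | 65.5% |
| 1.5 | −0.4 | 22.1% | 66.0% |

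In the last row the expected sign is reversed. With equal effects, raising the effect to 1.2 SD gives 4.9% against 94.6%, and raising the correlation to 0.9 gives 4.9% against 99.9%. A larger effect or a more stable measure therefore does not rescue the screen.

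**3. If the change score were also used as the mediator.** The protocol does not say this, so the step is conditional. Further assumptions: 10 patients per chaplain, patient outcome = 0.5 × the chaplain's T1 score + N(0,1), no direct effect, and consults before the delayed-start group's CBCT. The true indirect effect is 0.8 × 0.5 = 0.40.

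- Early group: slope of outcome on T1–T0 = 0.5 × 0.4/0.8 = 0.25
- Delayed group: T3–T2 shares no visit-specific variation with T1, so the slope is 0
- Pooled slope with equal groups = 0.125
- Indirect effect = 0.125 × (0.8 − late effect), which is 0.10, 0.05, 0.00 and −0.05 for the four rows above; simulated 0.097, 0.051, 0.002 and −0.050
- T1 score in both groups: 0.8 × 0.5 = 0.40; simulated 0.399
- T1–T0 in both groups: 0.8 × 0.25 = 0.20; simulated 0.199

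With equal effects the group coefficient stays at about 0.40 after adjustment, so the protocol's criterion would report no mediation. Full recovery with T1 reflects a model without measurement error. A separate simulation with test-retest reliability of 0.5 to 0.9 and a true indirect effect of 0.24 gave 0.12 to 0.22 with T1 and 0.00 with the mixed change score.

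**4. Timing of consults.** Aim 4 says "Upon completion of their training program, chaplain residents will provide spiritual consults to patients throughout the Emory hospital system", while Procedures says "During their training program, chaplain residents will provide spiritual consults to patients throughout the Emory hospital system". Procedures also places the delayed group's CBCT about midway through the year in one paragraph and at the end of the residency in another. The comparison requires delayed-start chaplains without CBCT, which puts their comparison consults before T3. The text does not fix the window further.

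**The case against.** The strongest reply is that the sentence defining the changes concerns the primary chaplain outcomes and does not mention mediation. That is correct. A reader might infer that the protocol prescribes T3–T2 as the delayed-start mediator, that no valid mediator exists at the consult, and that mediation must come out as zero for half the patients. The documents support none of this:

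- The mediation text names no visit or change score, and a statistical analysis plan may supply one.
- All residents are assessed at all four times, so scores earlier than T3 exist for delayed-start chaplains.
- Zero requires equal early and late effects, which Aim 3 treats as an open question.
- The split of the 300 patients is not given.

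Two further points have weight. The entry condition is not expressly tied to the Data analysis contrast, and an analyst could use the Aim 1 comparison instead. Self-reported compassion is not named among the primary outcomes, so the link is firmest for empathic accuracy. Aim 5 is also exploratory within a pilot.

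What the reply does not remove is the stated rule. The Data analysis section says how the CBCT effect is examined, uses the same expression for timing, and makes entry to the mediation model depend on a CBCT effect. A later plan faithful to that section would inherit the error, and one that followed Aim 1 would contradict the section.

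**Conclusion.** The point holds for the screen. The contrast given in Data analysis cannot show that CBCT changed a chaplain measure when training works equally well early and late, and it conflicts with Aim 1. Under the stated assumptions, about 5% of trials with a truly affected measure would admit it, against about 66% with the Aim 1 contrast. These percentages depend on the assumed effect, correlation and group sizes. The cancellation under equal effects and equal drift does not. With unequal effects the contrast is biased and can reverse sign.

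The claim about the mediator itself is conditional. If the same change score were used, T3–T2 would be measured after the comparison consults and would include training those chaplains had not yet had. The number of patients affected is not stated. Because the aim is exploratory this does not threaten the main chaplain comparison of Aim 1, but it should be corrected before the mediation analysis is run.

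**What to change.** In the mediation paragraph of Data analysis, state two things:

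- (a) Whether CBCT changed a chaplain measure is judged by the Aim 1 contrast: T0 to T1 in both groups, or T1 adjusted for T0.
- (b) The chaplain mediator is the score at the last assessment before the patient's consult and, for comparison patients, before the delayed-start group's CBCT, adjusted for T0. T3–T2 is not used for comparison patients.

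Keep (T1–T0) − (T3–T2) for the timing question only. Reconcile the two statements on when consults take place (Aim 4 and Procedures) and the two on when the delayed-start group receives CBCT (both in Procedures), so that the visit in (b) can be identified for each patient.

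The cost is one or two sentences plus the reconciliation. No new data are needed, because every resident is already assessed at T0, T1, T2 and T3.
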